#### Criteria for discontinuing or modifying allocated intervention {11b}

Participants may choose to stop the HIFT intervention for any reason. There are no special criteria for modifying the allocated intervention. Modification of the exercises within the intervention will be determined on an individual basis if a participant cannot perform the exercise properly. An alternative exercise will be chosen that targets the same muscle group and performed at the same target intensity.

#### Strategies to improve adherence to intervention {11c}

To improve adherence, HIFT exercise will be performed in small groups (2–5 people), which will remain the same throughout the 12-week intervention [82]. Additionally, all HIFT exercises will be facilitated by a CMES or their specifically trained exercise personnel, who will provide accountability, encouragement, and motivation.

#### Relevant concomitant care permitted or prohibited during the trial {11d}

To isolate the effects of the intervention alone, all participants will complete a physical activity and diet questionnaire [70, 71] prior to the start of the study. Participants will be asked to maintain the same behaviors throughout the study, then fill out the questionnaires midway and after the study to verify. Participants will be informed that any additional dietary and exercise interventions will be prohibited throughout the study.

#### Provisions for post-trial care {30}

Understanding that daily physical activity alone can improve health in sedentary populations, upon completion of the study, all participants will be encouraged to continue the regular exercise.

### Outcomes {12}

#### Primary outcomes

##### Blood analysis

Baseline and post-training blood analysis will be measured via venipuncture of the antecubital vein. Five milliliters of blood will be drawn for the lipoprotein metabolism profile (LMPP), 1 mL will be drawn for insulin, 1 mL will be drawn for glucose, 1 mL will be drawn for HbA1c, and 1 mL will be drawn for hematocrit. The LMPP consists of an ApoB count, Lp[a] count, and cholesterol and triglyceride content of each lipoprotein subclass (VLDL, LDL, HDL). Hematocrit is calculated to adjust for plasma volume changes applied to the cholesterol and triglyceride content measures. Glucose and insulin measures will be used to calculate insulin resistance (IR) using the homeostatic model assessment (HOMA) [83, 84]. For each variable, individual change from baseline will be calculated. Data will be aggregated as mean ± standard deviation (SD) for each dose group as well as for male and female subgroups with each dose groups. The mean change ± SD for each variable will be compared between the 3 dose groups and subgroups.

##### Endothelial function

Baseline and post-training endothelial-dependent vasodilation of the non-dominant forearm will be measured using venous occlusion strain gauge plethysmography (EC6 Strain Gauge Plethysmography System & Rapid Cuff Inflation System, Hokanson Inc., Bellevue, WA). Basal endothelial function will be measured for 5 min. During 5 min of reactive hyperemia, peak forearm blood flow (FBF) and 30-s area under the curve blood flow will be quantified. For each variable, individual change from baseline will be calculated and aggregated as mean ± SD for each dose group and subgroups. The mean ± SD for each variable will be compared between the dose groups and subgroups.

#### Secondary outcomes

##### Body composition

Baseline and post-training body composition will be measured via dual X-ray absorptiometry (DEXA). Individual change in total fat mass and lean mass from baseline will be calculated and aggregated as mean ± SD for each dose group and subgroup. The mean ± SD will be compared between the 3 dose groups and subgroups.

##### Self-perceived fitness

Baseline and post-training self-perceived fitness will be measured using the International Fitness Scale (IFIS) [85, 86]. This scale contains five questions with a Likert-type answering option (very poor, poor, average, good, and very good) associated to the elements of physical fitness: cardiorespiratory endurance, muscular strength, speed-agility, and flexibility. Individual change from baseline will be calculated and aggregated as mean ± SD for each dose group and subgroup. The mean ± SD will be compared between the 3 dose groups and subgroups.

##### Graded exercise test

Baseline and post-training cardiorespiratory fitness will be measured via a graded exercise test (GXT) on a power treadmill (CT850, Spirit Fitness, Jonesboro, AR). The GXT will begin with a 5-min warm-up at a self-selected pace, gradually reaching the pace they will maintain throughout the test. A modified Balke and Ware protocol will be used where participants will maintain their constant speed, and incline will be increased by 1% each minute until volitional exhaustion [87]. Maximal HR, VO_2_, and workload will be recorded via HR monitor (Polar F1, Polar USA, Warminster, PA) and metabolic cart (OxyCon Mobile, CareFusion Respiratory Care, Yorba Linda, CA). Participants will rest passively for 20 min after the completion of the GXT, then perform a verification trial to confirm VO_2max_ [88–90]. For the verification trial, participants will walk on the treadmill at a workload of 105% of their maximal workload during the GXT (last fully completed stage) until volitional exhaustion. If the VO_2max_ of the verification bout and GXT are within ± 3%, true VO_2max_ will be considered achieved [88, 90]. If participants are unable to reach VO_2max_, they will be asked to repeat the trial after a 24-h rest. Individual change from baseline will be calculated and aggregated as mean ± SD for each dose group and subgroup. The mean ± SD will be compared between the 3 dose groups and subgroups.

#### Tertiary outcomes

##### Exercise questionnaires

To assess the participant’s level of “enjoyment” and “intention to continue” their allocated HIFT intervention, a questionnaire will be administered post-training. For enjoyment assessment, the Physical Activity Enjoyment Scale (PACES) will be used [91]. The PACES is an 18-item, 7-point, bipolar rating scale. For the intention to continue assessment, two additional items will be added regarding (1) how likely the participant would continue performing that modality (0 = very unlikely, 10 = very likely) and (2) how many days per week the participant would consider performing that modality (0–7 days) [92, 93]. Data will be aggregated as mean ± SD for each dose group and subgroups. The mean ± SD will be compared between the 3 dose groups and subgroups.

#### Participant timeline {13}

Upon recruitment, participants will meet with the primary investigator and provide informed consent and health history. Next participants will be screened for the inclusion criteria at the HAP Lab at WCU. During the screening visit, participants’ height, weight, waist circumference, abdominal height, resting HR, resting BP, and resting SpO_2_ will be measured. Additionally, participants will be measured for a fasted basic blood lipid and glucose panel. Next, participants will complete a physical activity and diet questionnaire (Full Block Questionnaire, NutritionQuest, 2014) [70, 71], and all included participants will be asked to maintain their self-reported diet throughout the entire study.

Participants will begin the study with a baseline GXT immediately after the initial screening. Next, baseline metabolic testing in the HAP Lab and GVH will take place 48–72 h after. This visit will consist of a 12-h overnight fast, baseline endothelial function testing at the HAP Lab, then metabolic marker bloodwork and body composition testing via DEXA at GVH. Additionally, participants will complete the IFIS to assess self-reported fitness [85, 86]. During the following 3 weeks, participants will visit the HAP Lab twice a week for exercise familiarization and adaptation. Participants will then be randomized into 1 of 3 exercise dose groups (HIFT1, 1 session per week; HIFT2, 2 sessions per week; HIFT3, 3 sessions per week) and be scheduled for their exercise sessions for the following 12 weeks. The 12 weeks of supervised training will consist of three 4-week phases, where intensity and duration of exercise are progressed each phase. After the last exercise session, participants will be scheduled for two post-testing visits. The first visit will consist of a 12-h overnight fast, endothelial function testing, PACES and exercise intention questionnaires, and IFIS questionnaire at the HAP Lab, then metabolic marker bloodwork and body composition testing via DEXA at GVH. This visit will be scheduled no sooner than 48–72 h after the final exercise session to ensure acute lipid or glucose responses are not influenced [14, 94–96]. The second visit, 24–48 h later, will consist of the repeated GXT on a treadmill from baseline testing. See Fig. 2 for the schematic illustration of research design and Table 3 for the schedule of the study period.

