#### Sample size {14}

The sample size was projected with a change in ApoB as the main outcome variable between HIFT1 and HIFT3. Power calculations (IBM SPSS v25 Armond, NY) assumed a 1:1 equal allocation between HIFT1 and HIFT3. The baseline mean and standard deviations from a previous study [97] and pilot studies for ApoB were ~ 129 ± 25 mg/dL in sedentary adults with elevated cardiometabolic risk. Collectively, using these data, we consider a 15% reduction in ApoB to be clinically meaningful within the HIFT3 group [98]. Assuming a power of 0.90, *α* = 0.05, and an effect size of *d* = 0.80, a paired samples one-tailed *t*-test sample size calculation revealed a sample size of 60 subjects (20 per group) will establish the superiority of HIFT3 versus HIFT1 for pre- to post-differences in the primary outcome ApoB. With an estimated 5% dropout rate, we will recruit 22 subjects/group to obtain the necessary sample size of 60. Therefore, a total of 60 men and women who meet the previously stated inclusion criteria will be recruited and randomized post-baseline assessments into one of the three intervention groups. Data will be collected in cohorts of 12, randomized into intervention groups. This will continue until 20 participants per intervention group have completed the study. This will accommodate dropout within cohorts.

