#### Recruitment {15}

Participants will be recruited via advertisement flyers posted in the communities of Gunnison County, social media, word of mouth, employee email lists of WCU and GVH, local newspaper and magazine ads, churches, and through physician referral among the Gunnison County health care providers. To account for the logistical capacity of data collection, participants will be recruited in cohorts of 12 (randomized into intervention groups) where each cohort will complete the entire study before the next cohort begins. This will continue until 20 participants per intervention group have completed data collection.

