## Data collection and management

### Plans for assessment and collection of outcomes {18a}

#### Primary outcomes

##### Blood analysis

Participants will visit GVH for fasted blood draws performed by a trained phlebotomist at baseline and 48–72 h after the exercise intervention. Venipuncture of the anti-cubital vein will be performed, and blood will be collected into heparinized tubes. Five milliliters of blood will be drawn for the lipoprotein metabolism profile (LMPP), 1 mL will be drawn for insulin, 1 mL will be drawn for glucose, 1 mL will be drawn for HbA1c, and 1 mL will be drawn for hematocrit. All blood collected for the LMPP, insulin, and glucose will be frozen at − 80 °C and sent to Mayo Clinic Laboratories in Denver, CO. All results will be communicated back to GVH. The LMPP consists of an ApoB count, Lp[a] count, and cholesterol and triglyceride content of each lipoprotein subclass (VLDL, LDL, HDL). Hematocrit is calculated to adjust for plasma volume changes applied to the cholesterol and triglyceride content measures. Glucose and insulin measures will be used to calculate insulin resistance (IR) using the homeostatic model assessment (HOMA) [83, 84].

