##### Endothelial function

Endothelial function will be assessed at baseline and 48–72 h after the last exercise bout of the intervention. Fasted, endothelial-dependent vasodilation of the non-dominant arm will be measured using venous occlusion strain gauge plethysmography (EC6 Strain Gauge Plethysmography System & Rapid Cuff Inflation System, Hokanson Inc., Bellevue, WA). To begin, forearm volume will be measured by the water displacement method. Then, the arm will be elevated to the level of their heart, a pneumatic cuff will be placed around the wrist and upper arm, and a strain gauge will be fixed around their lower arm. Once all measuring devices are attached and ready, the contralateral arm will be used to measure HR and BP until stable resting values are obtained (after 15 min of supine quiet rest). Next, basal blood flow will be measured for 5 min. The wrist cuff will be inflated to 220 mmHg, and the upper arm cuff will cycle between 50 and 0 mmHg every 8 and 7 s for the entire 5 min. Then, the brachial artery will be occluded for 5 min at a pressure of 220 mmHg. At the 4-min mark of the occlusion period, the wrist cuff will be inflated to 220 mmHg again. At the end of the occlusion period, the upper arm cuff will be deflated to assess reactive hyperemia for 5 min. Peak forearm blood flow and 60-s hyperemia blood flow will be quantified.

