#### Secondary outcomes

##### Body composition

Participants will visit GVH to be measured for body composition via dual X-ray absorptiometry (DEXA) at baseline and 48–72 h after exercise intervention.

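### Post-testing is tied to the last exercise session, and no readable text has participants who stop early tested at week 12

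*Protocol article*

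**What the plan says.** All places are in the Protocol article.

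- **Timing tied to the session.** Participant timeline {13}: "After the last exercise session, participants will be scheduled for two post-testing visits". Endothelial function, under {18a}: "Endothelial function will be assessed at baseline and 48–72 h after the last exercise bout of the intervention".
- **Timing tied to the intervention.** Blood analysis, under {18a}: "Participants will visit GVH for fasted blood draws performed by a trained phlebotomist at baseline and 48–72 h after the exercise intervention". Body composition, under {18a}: "at baseline and 48–72 h after exercise intervention". The exercise questionnaires under {18a} use the same kind of anchor.
- **Stopping.** Section {11b}: "Participants may choose to stop the HIFT intervention for any reason". It does not say what happens to that person's outcome assessments.
- **Retention.** Section {18b}, whose title covers complete follow-up, describes supervision and encouragement at sessions and material handed over at the end of the trial.
- **Recruitment.** Sample size {14}: "With an estimated 5% dropout rate, we will recruit 22 subjects/group to obtain the necessary sample size of 60". Recruitment {15}: "This will continue until 20 participants per intervention group have completed data collection".
- **Analysis.** Section {20a} restricts the analysis to participants who complete at least 80% of the exercise and whose diet and activity habits stay the same. If non-adherence occurs, {20c} adds an intention-to-treat set of everyone randomised. A linear mixed model is named for missing outcomes; imputation is left as a possibility.
- **Status.** Section {31c} presents the article as the complete protocol.

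**The concern.** The intention-to-treat set is the plan's own check on an analysis that selects by adherence. It is useful only if outcomes exist for people who did not adhere. Those who attend few sessions but stay to the end would have them. Those who stop early might not, because the two clearest timing statements start the clock at the last session or bout, and the recruitment rule counts completers instead of following everyone randomised.

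The mixed model does not close the gap. Each outcome has one baseline and one post-training value, so a stopper without a post-test contributes a baseline only, and the model treats that person as having changed like similar completers. The enjoyment and intention items have no baseline at all, so an untested stopper contributes nothing to them. Blood not drawn at week 12 cannot be recovered later by any analysis plan.

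**Working it through.** **Tracing one participant.** Take someone in HIFT3 who stops in week 3.

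1. Read literally, {13} and the endothelial section place the post-test days after that last session, in about week 3 or 4. The aims are framed as effects after a 12-week programme, so this is not the planned outcome.
2. If instead the person is not called back, there is no post-test.
3. The blood, DEXA and questionnaire wording can also be read as the end of the 12-week programme. That would give a week-12 value, but the text does not settle it.
4. Under 1 or 2, {20c} includes the person in the intention-to-treat set without a valid week-12 value.

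**Inputs from Sample size {14}.** ApoB 129 ± 25 mg/dL; 15% reduction in HIFT3 taken as meaningful; 5% dropout; 20 completers and 22 recruits per arm.

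**The plan's dropout step.** 20 / (1 − 0.05) = 21.05, rounded up to 22. This reproduces. The 20 is taken as given.

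**Assumptions not in the documents.** Stoppers keep no benefit and have no post-test; HIFT1 falls by 5 mg/dL; pre-post correlation r = 0.7. Ranges are shown below.

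**One arm (HIFT3).**
- Fall in completers: 0.15 × 129 = 19.35 mg/dL.
- Overstatement = proportion stopping × benefit lost.
- Planned 5%: 0.05 × 19.35 = 0.97 mg/dL; true mean fall 19.35 − 0.97 = 18.38.
- Per stopper: 19.35 / 22 = 0.88 mg/dL. Two of 22, the margin between 22 and 20: 1.76 mg/dL.
- If stoppers keep half the benefit: 0.48 and 0.88 mg/dL.
- SD of change = 25 × √(2(1 − r)) = 19.36 at r = 0.7; arm standard error = 19.36 / √20 = 4.33.
- 0.97 / 4.33 = 0.22 standard errors (0.17 at r = 0.5, 0.39 at r = 0.9).
- 1.76 / 4.33 = 0.41 (0.31 to 0.70).

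**Contrast, HIFT3 versus HIFT1.**
- Completers: 19.35 − 5 = 14.35 mg/dL.
- Equal 5% stopping: 18.38 − 0.95 × 5 = 18.38 − 4.75 = 13.63; overstatement 0.72 mg/dL.
- Standard error = 19.36 × √(2/20) = 6.12; 0.72 / 6.12 = 0.12. At r = 0.5 and 0.9 the standard errors are 25.0 × √0.1 = 7.91 and 11.2 × √0.1 = 3.54, giving 0.09 and 0.20.
- With a HIFT1 fall of 0 or 10 instead of 5: 0.05 × 19.35 = 0.97 and 0.05 × 9.35 = 0.47 mg/dL.
- Two of 22 stopping in HIFT3 and none in HIFT1: 17.59 − 5 = 12.59; overstatement 1.76 mg/dL, or 0.29 standard errors.

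**People affected.** 22 × 0.05 = 1.1 to 22 − 20 = 2 per arm, so about three to six in total.

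**The case against.** The case against has real weight.

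- **It argues from silence.** No sentence excludes stoppers from post-testing, and {11b} speaks of stopping the intervention, not of leaving the study. This stands, and it rules out a stronger reading that a reader might infer: that the plan drops stoppers from follow-up. The text does not say so. What it does is fix a time anchor that works badly for them and leave the rest open.
- **Several timings may mean the end of the programme.** The blood, DEXA and questionnaire wording allows this, and Recruitment {15} has each cohort finish before the next begins. This stands as an ambiguity. It does not remove the session-based wording in {13} and the endothelial section.
- **The schedule cannot be seen.** Table 3 is laid out by week, according to its footnote, and neither it nor Fig. 2 is readable here. They might show a fixed week for post-testing. The point therefore rests on the readable text only.
- **The article may condense, or an analysis plan may cover it.** This does not stand. The article calls itself the full protocol, and who is invited to a visit is a matter of conduct that an analysis plan cannot repair.
- **The effect is small.** This stands, as the figures show.

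A reader might also infer that stopping will be heavier in HIFT3, because the research hypotheses expect enjoyment to fall as dose rises. The documents give no stopping rates by arm, so uneven stopping is a possibility and no more.

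**Conclusion.** The point holds as a minor one. Two sections anchor post-testing to the last session or bout, three others are ambiguous, and no readable text provides for week-12 testing of randomised participants who stop early. Followed literally, the conditional intention-to-treat set and the post-only enjoyment and intention items would lack valid week-12 values for them.

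At the plan's own dropout rate the ApoB effect is well under half a standard error, even if stoppers keep no benefit. It would be larger only with more stopping than planned or with stopping that differs between arms. The ratios to standard errors depend on the assumed correlation, and the contrast also on the assumed HIFT1 fall.

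A reader might infer that the trial's main result is biased by this. The documents do not support that: the analysis in {20a} is confined to participants with at least 80% completion and would be the same either way. Only the check on that analysis, and the completeness of the tertiary items, are affected.

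**What to change.** Amend the wording in {11b}, {13}, {18a} and {18b}:

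- State that stopping exercise is not the same as leaving the study.
- Invite every randomised participant who has not withdrawn consent for follow-up to the existing post-test visits in the week after training week 12.
- Keep the 48–72 h gap for those still training, and record the date of each participant's last session.
- Make the maximal treadmill test optional for anyone who stopped for a medical reason or declines it. It includes a verification bout in which "participants will walk on the treadmill at a workload of 105% of their maximal workload during the GXT", which may be unsuitable for them. The blood, endothelial, DEXA and questionnaire assessments can go ahead without it.

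The cost is a few sentences and the existing visits for about three to six more participants in total, with no new procedures. Some will decline, so missing data are reduced, not removed. Stoppers would answer the enjoyment items longer after their last session, and the recorded date lets the report show this.

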## Methods

### Study setting {9}

The intervention and measurements will take place in Western Colorado University’s (WCU) High Altitude Performance (HAP) Laboratory and Gunnison Valley Health Hospital (GVH) in Gunnison, CO, USA.

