#### Intervention description {11a}

For 3 weeks prior to the 12 weeks of training, participants will undergo exercise familiarization 2 days/week. Participants will then be randomized into 1 of 3 exercise dose groups (HIFT1, 1 session per week; HIFT2, 2 sessions per week; HIFT3, 3 sessions per week). Then, 12 weeks of supervised training will commence consisting of three 4-week phases, where intensity, duration of exercise, and recovery time are progressed each phase.

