#### Implementation {16c}

[name] will communicate the treatment allocation to each participant via a personal email. This communication will only occur after the participant has been enrolled, completed baseline testing, and completed the adaptive period. Thus, allocation communication will be conducted without any influence on recruitment and enrollment.

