## Assignment of interventions: blinding

### Who will be blinded {17a}

All data collection sheets and data analysis will be coded by the investigator assigning the interventions in order to blind the primary investigator and research assistants from intervention allocations. Data analysis, data collection, and exercise training will be conducted by the primary investigator and research assistants but not the investigator conducting the allocations. Due to the nature of the intervention, participants will not be blinded to their allocation but are strongly encouraged not to disclose their allocation or the allocation of other participants.

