### Plans to promote participant retention and complete follow-up {18b}

Exercise supervision and encouragement will take place during every session of the intervention to promote participant retention and safety. Participants will be given a copy of all HIFT workouts and personal health data at the end of the trial which may serve as an incentive to continue the habit of regular exercise on their own.

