### Confidentiality {27}

Any potential and enrolled participant information will be kept confidential, only identifiable by primary investigators. Codes will be used instead of names on all documents. For all data collected at WCU and GVH, the standard HIPAA regulations and procedures will be followed. Each participant’s information will be combined with other people taking part in the study when results are shared or presented in materials.

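### Enjoyment and intention-to-continue forms are completed in the training lab, with data collection assigned to the roles that deliver and motivate training and no private return stated, so favourable answering cannot be excluded and could work against the hypothesised inverse dose-response.

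*Protocol article*

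**What the plan says.** All references are to the protocol article.

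- **Place and time.** Participant timeline {13} schedules "PACES and exercise intention questionnaires, and IFIS questionnaire at the HAP Lab" at the first post-training visit. The questionnaire paragraph under {18a} puts PACES and the two intention items 48–72 h after the intervention. They are not given at baseline.
- **Training site.** Study setting {9}: "The intervention and measurements will take place in Western Colorado University’s (WCU) High Altitude Performance (HAP) Laboratory", with the hospital as the second site. The familiarisation visits are also at the HAP Lab.
- **Roles.** Who will be blinded {17a}: "Data analysis, data collection, and exercise training will be conducted by the primary investigator and research assistants". The investigator who does the allocation is excluded from this work. Participants know their dose.
- **What trainers do.** Under {11c}, sessions are led by exercise personnel "who will provide accountability, encouragement, and motivation". Under {18b}, "Exercise supervision and encouragement will take place during every session of the intervention".
- **Dose.** Intervention description {11a}: "HIFT1, 1 session per week; HIFT2, 2 sessions per week; HIFT3, 3 sessions per week", for 12 weeks, after three weeks of familiarisation twice a week in all arms.
- **Data handling.** Data management {19} codes names on assessments and has the principal investigator enter the data. Confidentiality {27}: "Any potential and enrolled participant information will be kept confidential, only identifiable by primary investigators"; it also requires codes in place of names on documents.
- **Hypothesis.** Objectives {7} expects enjoyment and intention to continue to fall as dose rises, and fitness to improve as dose rises.

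**The concern.** PACES and the intention items ask participants to judge the programme. Here the judgement is given in the room where they trained, within a visit run by the roles that coached them. A wish not to disappoint familiar staff would push answers upward. This is reporting bias on the participant's side. It differs from assessor bias, and blinding the staff to dose would not remove it.

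A shift common to all arms would cancel in the between-arm comparison. A shift that rises with contact would not, because contact is set by the randomised dose. It would lift HIFT3 most, opposite to the hypothesised gradient. A flat result could then be read as three sessions a week being as well accepted as one. That bears on the abstract's stated purpose of learning whether this form of exercise is likely to ease the barriers to exercise. With no baseline PACES score, there is nothing in the data to adjust for a participant's tendency to answer kindly.

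**Working it through.** The protocol gives no effect size, SD or power for PACES, so there is no figure of its own to reproduce.

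**1. Supervised contact by arm**

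Inputs: 12 training weeks at 1, 2 or 3 sessions a week ({11a}); familiarisation of 3 weeks × 2 visits = 6 in every arm, which may be extended for individuals.

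| Arm | Training sessions | With familiarisation | Ratio to HIFT1 |
|---|---|---|---|
| HIFT1 | 12 × 1 = 12 | 12 + 6 = 18 | 1 |
| HIFT2 | 12 × 2 = 24 | 24 + 6 = 30 | 30/18 = 1.67 |
| HIFT3 | 12 × 3 = 36 | 36 + 6 = 42 | 42/18 = 2.33 |

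Contact rises with dose. On all supervised visits the HIFT3:HIFT1 ratio is 2.33, against 36/12 = 3 on training sessions alone.

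**2. Do the stated arrangements separate rating from training?**

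- Place: the same lab.
- Roles: data collection and training are assigned together in {17a}, with no exception for questionnaires.
- Return of the forms: no sealed, remote or independent route is described.
- Coding: it removes the name from the paper. It does not change who is present when the form is completed or handed back.
- Data entry: by the principal investigator, to whom participants are identifiable under {27}.

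Nothing stated keeps these answers away from the training team.

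**3. What an assumed bias would do**

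Method: two-sample t-test of HIFT3 against HIFT1, n = 20 completers per arm ({14}), two-sided 0.05, 2 × 20 − 2 = 38 degrees of freedom. Power comes from the noncentral t distribution with noncentrality d × √(n/2) = d × √10. The observed difference is the assumed true difference minus the assumed extra favourable answering in HIFT3.

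| True difference (assumed) | Extra bias in HIFT3 (assumed) | Observed d | Power |
|---|---|---|---|
| 0.8 SD | 0 | 0.8 | 69% |
| 0.8 SD | 0.2 SD | 0.6 | 46% |
| 0.8 SD | 0.4 SD | 0.4 | 23% |
| 0.8 SD | 0.8 SD | 0 | 5% |
| 0.5 SD | 0 | 0.5 | 34% |
| 0.5 SD | 0.2 SD | 0.3 | 15% |
| 0.5 SD | 0.4 SD | 0.1 | 6% |

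The table shows sensitivity only. Both assumed columns come from outside the protocol. The t-test is also a stand-in: {20a} lists median, mode and interquartile range for PACES, while the outcome section {12} compares means.

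**4. Direction for each form**

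- PACES and intention items: expected to fall with dose; the bias raises the top-dose scores and opposes the hypothesis.
- IFIS (self-perceived fitness, measured at baseline and post-training): fitness is expected to rise with dose; the same bias would exaggerate the hypothesised pattern.

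**The case against.** - **Who handles the form is not stated.** No section names the person who hands out or collects PACES, and {17a} describes overlap by role. A reader might infer that each participant's own trainer takes the form back. The protocol does not say so. What stands is narrower: the roles coincide, and no separate route is provided.
- **Coding is already planned.** Names are coded on assessments, and the allocating investigator codes the data collection sheets. This protects identity on paper and deserves credit. It does not stop a participant from expecting that familiar staff will see the answers.
- **Growth with contact is assumed.** All arms meet the staff at six visits before randomisation, so any courtesy effect could already be at its ceiling and equal across arms. This objection stands in full; the direction is conditional.
- **Real enjoyment may rise with coaching.** Supervision and encouragement are part of the intervention, so higher enjoyment from more contact would be a genuine effect. Private completion would not remove that effect; it would make it easier to tell from politeness.
- **The trial is small anyway.** With a true difference of 0.5 SD and no bias, power is 34%, so a flat result is already the likelier outcome. Sample size is then the main reason not to over-read it.
- **Consequence is low.** These are tertiary outcomes in a trial described as exploratory.

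**Conclusion.** The point holds as an inexpensive improvement to the design. The protocol places the enjoyment and intention ratings in the training lab, gives data collection to the training roles, and states no private return. Favourable answering is therefore plausible, and if it grows with contact (18, 30 and 42 visits) it would work against the hypothesised inverse dose-response.

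Stronger readings are not supported:

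- A reader might infer that the bias is established or known to increase with dose. The protocol shows only that contact increases.
- A reader might infer from the illustration that a fixed share of the true effect is hidden, for example 0.2/0.5 = 40% or 0.4/0.5 = 80%. Those ratios are one assumption divided by another.
- A reader might extend the masking argument to the IFIS. There the bias would inflate the expected pattern.

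The primary ApoB comparison is unaffected.

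**What to change.** 1. In Participant timeline {13} and the questionnaire paragraph of {18a}, state that PACES and the two intention items are self-completed out of sight of training staff. They are then returned under code, in a sealed envelope or by electronic form, to the investigator not involved in training. That person already "will communicate the treatment allocation to each participant via a personal email".
2. In Data management {19}, state that this investigator, in place of the principal investigator, enters these forms.
3. Tell participants that trainers will not see individual answers. For this to be true, the scores should reach the analysis data set under a code that training staff cannot link to a name.
4. Handle the IFIS the same way at both visits for consistency, noting that its possible bias runs in the opposite sense relative to its hypothesis.
5. Concealment mechanism {16b} keeps this investigator out of assessments, so add a short exception for receiving and entering self-completed forms.

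Cost: envelopes or a simple web form, a few sentences of text, and entry of 18 + 2 = 20 items for 60 completers, which is 1,200 values on paper and none by hand if electronic. No extra visit or staff is needed. The small downside is that missing items cannot be queried on the spot; required fields in an electronic form would largely avoid this. The change must be in place before the first cohort's post-training visit, because it cannot be applied to forms already collected.
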